**5. Randomization at First Group Session (Session 1)**

When participants arrive at the appointed time for their first group session (Session 1), they will be randomly assigned to either the intervention group or the comparison group. At least 12 people must attend the first session for the cohort to begin (average of 5 per group - allowing 10 to be randomized will result in one group only having 4 participants much of the time). If less than 12 people attend, the cohort will be rescheduled.

Block randomization by HIV status will be generated by an established computer-based program on a staff computer (laptop or desktop) after all participants check in. The computer will generate a list of randomized assignments to the two arms (intervention and comparison) for all men who have checked in by the designated time.

Based on experience with previous studies and the focus group and pilot phases of this project, we expect high risk HIV-negative men to be harder to recruit than high risk HIV-positive men. Thus we plan to use a 4-person block design (2 in Group A, 2 in Group B) to attempt to balance HIV-status between groups in each cohort (Table 4). Because we expect that it will be easier to enroll HIV-positive men into the trial, we plan to use randomly-generated 4 and 6 person blocks to more closely approximate pure randomization, however the first block will be a block of 4 to parallel the 4-block design for HIV-negative men to ensure at least 2 men from each serostatus in each cohort arm.

Every effort will be made ahead of time to schedule for the randomization session (Session 1) at least 4 men of each HIV status. **This is done to minimize the probability of one man of either serostatus being alone in one of the arms.** The exception to this rule if only 1 or 3 persons of a particular serostatus show up for Session 1; it is also possible that if only two people of a particular serostatus arrive at Session 1, they could be split and end up alone in each of the two arms with a 4-block design, in which case he will be randomly assigned to a group in the same process as the rest of the cohort is assigned. Following the group assignment procedure, the computer will randomly assign the two groups (A and B) to type of arm (intervention or comparison) so that group assignment process is blinded up to the final step.

The study coordinator will supervise the randomization process. At the time of the visit, staff will confirm identity, study ID number and that consent was obtained. Once the participants are checked in, the computer will randomly assign the participants to an arm, which will be recorded by staff in the locator database.

A participant may miss up to two confirmed randomization appointments due to circumstances under their control before being dropped (staff judgment).

**Table 4. Plan for block randomization by HIV status: 4-block assignment for HIV-negative men and initial 4-block assignment followed by randomly generated 4- and 6-person block assignment for HIV-positive men (read down columns).**

**HIV+ HIV-**

Cohort1(n=9) Cohort1(n=5)

A A

A B

B A

B B

--- ---

A B

B

A

B

A

Cohort2(n=9) Cohort2(n=8)

B A

A B

A B

B A

--- ---

A B

A A

A A

B B

B ---

Cohort3(n=8) Cohort3(n=6)

A B

B A

B B

A A

--- ---

B A

B A

A

A

---

## 6. Intervention and Comparison Arm Sessions

In addition to **one** baseline assessment session, both randomized arms of the study – intervention and comparison – consist of **six** 2-hour group sessions led by two facilitators. Each participant will be asked to attend **six** session appointments during the first two months followed by **three** 2-hour follow-up assessment sessions, at 3, 6 and 12 months after their final group session. Thus, each participant will attend a **total of ten appointments** during the length of the study, over a 14-month span of time. Two trained and experienced (defined as having experience counseling and facilitating groups and having experience working with populations targeted in this study, i.e., both HIV-positive and -negative SUMSM from a variety of racial and ethnic backgrounds) facilitators will present the intervention or comparison material and activities for the full six group intervention sessions. One or two staff may periodically observe the group sessions and take notes for facilitator and content quality assurance purposes. Content of the intervention arm by session is presented in Appendix RR. Content of the comparison arm by segment (there are twelve 1-hour segments; two segments per group session) is presented in Appendix SS. In both study arms, a resource table will be used at the back of the room in which the sessions are being held. This table will contain printed materials and is intended to provide additional information to participants that desire additional information or resources on certain topics. In the intervention arm, this will include information regarding sexual risk reduction, alcohol and drug treatment programs, as well as mental health services. In the comparison arm, this will include information regarding topics covered in the videos (e.g., local community resources regarding adoption services, spirituality, ethnic and racial community organizations etc.).

At the end of the first group session, the date and time of the subsequent group sessions will be determined. It is expected that group sessions will be held once a week on consecutive weeks, preferably at the same time and day of the week. If holidays interfere, alternative dates will be established.

Participants will be encouraged to attend every session. If a participant misses a session, they will be allowed to attend subsequent sessions, although missed sessions will be documented. If a participant is late for a session, they will be allowed to participate in that session and the extent of their lateness will be recorded in their file in order for researchers to later assess the extent of the content missed (for intervention exposure purposes); participants who arrive late will receive reimbursement in accordance with rules explained to them and described elsewhere in this document. Facilitators will not take significant time away from the group to bring people up to speed on missed content.

**7. Quality Assurance**

As described earlier, each intervention and comparison group at the time of randomization will have a minimum of 5 and a maximum of 10 participants (average, 7). The groups will be audio-recorded and transcribed as needed, and periodically observed, for purposes of facilitator supervision and content quality assurance. The primary purpose of taping the group sessions is to provide an additional and more objective source of assessment information for monitoring and evaluating the quality of the intervention and to be certain the curricula are being implemented as intended. Further analysis (e.g., content analysis) of the tapes may be undertaken to better understand behavior and motivations of study participants and how the study materials may work to facilitate change. As part of the informed consent process, participants will be told about the role of the observers, audio taping, and transcription.

Observers or reviewers of tapes will periodically sit in and take notes during the sessions (approximately 10% of the sessions), and observers or reviewers of tapes will write a brief summary report after they sit in on a group session (see Appendices TT for Session Observer Summary Form). This is done for purposes of both quality assurance (across sites) and facilitator supervision (within sites) to examine the content and process of the sessions for purposes of facilitator supervision and to be sure the curricula are being implemented as intended. Feedback regarding session activity will be discussed among appropriate project staff to ensure adequate and appropriate delivery of intervention content and process; supplemental training of facilitators will be given as needed. Quality assurance across sites consists of two sites (including CDC) reviewing one tape from each cohort arm of each site. Copies of tapes are transferred between sites by FedEx or other courier service, and returned to the original site after reviews are completed. Discussion of the supervisory issues and quality assurance (QA) reviews take place during biweekly QA committee conference calls.

Assessment and counseling staff will observe ACASI and HIV counseling and testing procedures and take note of any problems that arise throughout the trial. Staff will also ask participants if they had any problems with ACASI immediately following completion of the survey. Staff will hold internal reviews and discussions about ACASI, HIV counseling/testing, and clinical/lab procedures during the trial so that recommendations for assessment and procedural improvements can be made on an ongoing basis.

**8. Follow-Up**

Participants will be scheduled for **three** follow-up visits, at 3, 6, and 12 months after their last session. All participants will complete an ACASI behavioral assessment regarding sex and drug risk behaviors and related psychosocial factors (Appendix OOb); this is a reduced version of the Baseline assessment with a few additional items about pre-exposure prophylaxis and methamphetamine use. In addition, participants who were HIV-negative at last testing will provide finger stick blood or oral swab samples for rapid HIV testing at the 12 month visit. Participants will be reimbursed $35 ($25 in NY) for the 3-month follow-up visit, $40 ($35 in NY) for the 6-month follow-up visit, and $50 for the 12-month follow-up visit (to maximize return at the final outcome point of the study, which comes a full 6 months after the prior follow-up visit). Participants who are tested for HIV infection (i.e., men who were HIV negative at last testing) will be given results of their rapid HIV test following procedures described earlier for the baseline assessment. Timing of follow-up visits is scheduled to allow site flexibility while still scheduling follow-up visits within a reasonable time span (see Figure 1).

Every effort will be made to ensure that follow-up visits are not conducted by staff who served as group facilitators (intervention or comparison arm) for that particular participant. This is done to avoid potential reporting bias that may occur when participants interact during assessment with facilitators with whom they worked during the intervention and comparison groups. When scheduling participants for follow-up visits, records will be reviewed to be sure that facilitators are not paired with their group participants.

Follow-up visits will be scheduled within a **two-week target window** based on participant availability and site capacity; visits may be scheduled either up to one week before or up to two weeks after the target follow-up date. Participants who miss an appointment within the target window or cannot complete the assessment at that time will be scheduled for an appointment outside of the target window, but within the acceptable window period. For the 3-month and 6-month visits, the acceptable window period will be one week before the start of the target window and two weeks after the target window.

1 Week

2 Weeks

2 weeks (3 & 6 month FU)

12 weeks (12 month FU)

**Target Window**

**Figure 1. Acceptable Follow-Up Assessment Window**

Every effort will be made by staff to ensure that participants are assessed in follow-up visits within, first, the target window, and second, the acceptable window. If it is not possible to assess within these windows, assessment will take place at whatever time possible with the primary intent of getting the participant back on track with their original 3, 6 and 12-month follow-up waves. A judgment call will be made as to how best to handle the situation by the staff given the particular circumstances for the individual participant and point in time that he contacted. For example, if a participant was out of the country during the 3-month window and eventually calls the site at the 5 month point, the staff person will assess participant willingness and ability to attend follow-up in the 6-month window and based on the individual participant either (a) schedule him for an assessment now and in a month, during the 6-month follow-up window (if the participant is willing and able to do both); (b) schedule him for the 6-months assessment only (if the participant is available then and unwilling to attend 2 follow-up assessments close to one another in the near future), or (c) schedule him for an immediate assessment only (if the other two options are not possible). This is done because data collected outside of a follow-up window are difficult to categorize for assessment purposes and thus are less desirable than data within 3, 6 and 12-month windows as defined earlier. For example, if data are collected at 5 months and at 6 months, the 6-month data will obviously be used for analyses in the 6-month wave, however the 5-month data will likely not be analyzed in the 3-month wave because (1) data were collected well after the 3-month wave and are actually closer in time to the 6-month wave, and (2) since we have 6 month data already, we won’t use the 5-month data (which also happens to overlap significantly with the 3-month behavioral assessment window). Alternatively, if data are collected at 5 months and it is not possible to assess the participant again during a 6 month wave, the 5-month data are preferred to no data at all. Thus, assessment of each individual situation and a judgment call are required of staff when participants are reached outside of a follow-up window. When a participant is assessed within the acceptable window for the 3-month assessment, there must be at least 90 days between the 3 and 6 month assessments.

For the 12-month assessment, there will be a two-week target window (one week before and after the 12-month date). The acceptable window for this final follow-up visit is longer, however: one week before the target window begins and 3 months after the target window ends. This final acceptable window is more generous because it is crucial that as many participants as possible participate in the final visit so that we can fully measure the potential impact of the intervention.

**9. Retention Efforts**

**Locator Information.** Participant locator and contact information (see below) will be collected and periodically updated in order to remind participants of their upcoming visits and enhance study retention. This information will be updated in a locator information database at the baseline visit, at the end of the intervention and atthe follow-up visits (3, 6, and 12 months). In addition, contact will be made at 9 months to update locator information. Staff will update the database with the new locator information, but they will not share this information with any other person or organization.

Whenever the project staff uses this information to try to locate a participant, they will identify themselves as being from the organization conducting the study. If staff contact friends, family members, or another approved contact person, they will tell the contact person that the participant is in a research study and has provided written permission to contact this person or organization only to obtain locating information. Staff will not reveal to the contact person what the study is about (HIV prevention) or that the study involves substance use or MSM.

The comprehensive database tracking system will hold all personal information for each participant, including contact information and scheduled and completed appointments (including appointment times and dates). These data will remain separate from the assessment data to protect participant confidentiality. The database will be able to automatically generate the following items at any given time: a list of reminder cards to be sent to participants, a list of participants who need to be contacted via telephone or other method, and a schedule of upcoming appointments. These items will be generated and processed on at minimum a weekly basis throughout the study.

Obtaining reliable locator data at the baseline appointment is essential to contact at subsequent visits. Informed consent to participate in the study should include an explanation by the recruiter that they are agreeing to provide contact information and do their best to voluntarily attend all study visits. As mentioned earlier, a locator form will be used to collect data to allow study staff to contact the participant and remind them of their next visit. Participants without a stable email or postal address, or phone number, may drop in at the study office to set up an appointment or to complete the visit.

Data on the Locator Forms (see Appendix UU), which vary slightly by study sight based on local procedures, include participant name and study ID; date and location of recruitment; address, phone numbers [home, work, cell] and e-mail addresses to contact the subject for the next study visit; name, address, and phone number of friends, family members, or other people who are likely to know how to contact them over the next 15 months (their relationship to the participant will be noted). Contact information may specify whether or not project mail can be sent to this address, and whether or not it is okay to mention the name of the study in a message. Participants will be asked to suggest the best way to contact them (e.g., phone or email; time of day to call and which number to try first). The locator form asks other ways to reach the participant, including café, bar, or club; if it is okay to come by their residence and leave a message; and whether the participant has other ideas how they could be contacted. This information will be obtained on a purely voluntary basis (i.e., not a requirement for participation in the study). However, staff will make a judgment call as to whether or not limited contact information is adequate for participation given the individual circumstances and potential for successful staff follow-through with the participant. For example, if a person does not have a phone or email address but they have received services regularly at a known agency for an extended period of time and indicate that study staff may contact them through the agency, then given other circumstances for the individual (e.g., an address, contact information for others close to them) a study staff person may consider this adequate contact information for the individual to participate.

**Retention before and during the group sessions.** Because participants for each cohort will be recruited over severalweeks, they will get a call or note from one of the project staff a few days before the first session. Participants will be asked at the end of the screening what would be the best way for us to remind them of the appointment. Some participants will have a phone and be willing to be called; others may wish to be contacted through e-mail. Those who do not prefer these modes of contact may be contacted through agencies where they receive services (by leaving a note) or through outreach workers going out into the communities where people live. In all cases, the participant will consent to be contacted in the manner used. If a participant consents to have a note left with agency staff, the note will be sealed. We will explain to participants that in all cases, a clear boundary exists between the research project and agency staff that prevents the sharing of information we learn about them during the research study with anyone at the agency.

Participant retention during the intervention will be enhanced in several ways. First, participants will be reimbursed for each session they attend (described earlier) to offset travel costs and for their time. At the beginning of each week, group leaders will give reminder calls to or send emails to remind them of that week’s sessions. In addition, if someone in either the intervention or comparison arm misses a session, the group facilitators will call or contact the participant to determine why a given session was missed and to try to encourage them to attend the next session. Participants will be asked to call the project if they are going to miss a session.

**Retention during the follow-up period.** Participant retention after the intervention will be enhanced in several ways. First, participants will be reimbursed $35, $40 ($25, $35 in NY) and $50 for 3, 6 and 12 month follow-up visits, respectively, to offset travel costs and time. The provision of a monetary reimbursement should enhance participation in the follow up visits. In addition, extensive procedures will be used to promote participant attendance at the follow-up visits. This is particularly important in an intervention trial, where high-levels of follow-up are required for examining the effectiveness of the intervention. At each follow-up visit (3, 6 and 12 months), and at 9 months after the final group session, subjects will be asked to update their locator information.

Letters will be sent out or phone calls will be made up to several weeks or more prior to the follow-up visit due date requesting that they contact the main office to confirm or reschedule an appointment, and reminder calls will be made within several days of the appointment. The letters (see Appendix UU) will thank the participants for being in the program, remind them of the date and time of their next follow-up appointment (in 3 or 6 months), and note the telephone number that can be called if rescheduling is necessary. The letters will be discrete with regard to the nature and purpose of the study. The letter will state that if they miss this visit, to please call to reschedule. Study staff will make three attempts over the window period (5 weeks for 3 and 6 month follow-ups; 15 weeks for 12-month follow-up) to contact participants who do not respond. Participants who do not respond and cannot be located during the acceptable window period are classified as having missed that visit. If staff are contacted by the participant after the acceptable assessment window period, a follow-up appointment will be scheduled nonetheless and the participant will be scheduled for the next follow-up visit according to their original follow-up schedule. Whenever possible, the next follow-up visit will be scheduled while the participant is in the office for the current visit. Once a participant is voluntarily enrolled in the study, staff will continue with contact attempts until a participant expresses the desire to be dropped from the study. For example, repeat no-shows within a particular follow-up window will continue to be rescheduled for follow-up until that particular window closes.

If a participant moves away from the original project city during the study, other arrangements will be made for follow-up. If the participant moves to a location close to another Project Mix site (i.e., Chicago, Los Angeles, New York City, San Francisco), project staff at the original city will attempt to gain approval from the participant to transfer contact and tracking information about the participant to the new city (see Appendix VV for release of information forms by site). The new city will need to receive informed consent from the participant, using the local consent form and consenting procedure. If written approval and consent are not obtained from the participant, or the participant moves to a location that is not close to one of the project cities, follow-up visits will be conducted over the phone by staff at the original project site. If the participant tested HIV-negative at baseline and moved to another project site during the study, the participant will be tested on site at 12-month follow-up as described in the protocol. If the participant tested HIV-negative at baseline and moved to a location other than a Project Mix site, the participant will not be asked to complete an HIV test as part of the study procedure. Similarly, safe and private alternative locations will be considered for follow-up assessment for local participants within a site who are unable to come to the office.

**Ascertaining reason for losses to follow-up.** A list of the study ID’s of lost participants will be maintained at each site, with disposition being recorded on the list when it is determined. In some cases, the study staff may learn that the participant has moved away; staff will continue to attempt to reach these participants for follow-up and make every reasonable effort to accommodate the participant in order to complete the follow-up assessment. Options for long-distance follow-up include staff-administered ACASI assessment over the phone; assessment coordinated through another Project Mix study site if the participant moved to a project city (Chicago, Los Angeles, New York, San Francisco). Relocation information may be provided by the participant, his or her contacts, or by the US Postal Service. Study letters sent to participants will be stamped with “forwarding and address correction requested”. This service is provided for 50 cents. At the end of each year of follow-up, sites may consult local or national death records or indexes to determine whether lost study participants have died.

Participants who are in substance abuse treatment or prison will be classified as such. Subjects may also refuse to complete any follow-up visits; these will not be combined with study losses, but classified as refusals. For some lost subjects, reason for loss will not be determined. At the end of the study, follow-up rates will be calculated.

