After successfully completing written consenting procedures, the participant will complete the baseline assessment on a computer in a semi-private location. The baseline assessment session of the trial consists of a 1-hour (approximately) Audio-Computer-Assisted-Self-Interview (ACASI)-administered survey of self-reported demographic factors, recent sexual and drug use behavior, and a number of potential cofactors of sexual and drug use behavior, including attitudes, beliefs, knowledge, traits and other psychosocial factors (see Appendix OO for the paper version of the ACASI baseline survey instrument). Staff will be present to assist the participant in getting started on the ACASI computer, which includes a set of practice items. Staff will remain easily accessible during survey completion to address any technical problems or to answer questions participants may have. Staff may periodically check in with the participant to inquire about any difficulties that may arise in completing the survey. However, to ensure privacy, the staff person will not directly observe the full process of completing the survey on the ACASI. Then staff will deliver HIV counseling and testing in a private location (see Appendix PP for baseline session flow).

*d) HIV Counseling and Testing.*

Following completion of the ACASI survey, the participant will receive counseling and complete rapid HIV testing (OraQuick or Rapid OraSure [if available at the time]) if they report receiving a negative result following their most recent HIV test or they self-report that they have not been tested or do not know their HIV-status. These participants will have the OraQuick finger-stick rapid HIV test (or Rapid OraSure oral swab HIV test, if available) administered consistent with instructions included in the test packaging (see Appendix QQ attachment: OraQuick Guide.pdf). These tests are CLIA-waived and include 3 steps before reading a result: (1) collecting a sample from a finger stick or oral swab using the specimen collection loop; (2) mixing the sample by inserting the loop into the developer vial; (3) testing the sample by inserting the test device into the developer vial and using a timer, allowing 20 minutes to pass (but no more than 40 minutes) before reading the result.

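### Some men who relocate give their follow-up outcomes to site staff by telephone, although the protocol says all complete ACASI; no rule masks the caller to arm, and the sections need reconciling.

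*Protocol*

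**What the plan says.** Protocol section 8 (Follow-Up) states the rule without exception: "All participants will complete an ACASI behavioral assessment regarding sex and drug risk behaviors and related psychosocial factors". Section 4 (Baseline Assessment Individual Session) explains what ACASI protects: "to ensure privacy, the staff person will not directly observe the full process of completing the survey on the ACASI".

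Section 9 (Retention Efforts) departs from this for some men who relocate. The trigger is: "If written approval and consent are not obtained from the participant, or the participant moves to a location that is not close to" (the sentence then refers to the four study locations). For these men "follow-up visits will be conducted over the phone by staff at the original project site". Later in the same section, under reasons for losses to follow-up, the route is described again: "Options for long-distance follow-up include staff-administered ACASI assessment over the phone". Men who move near another project city and agree to transfer are followed there instead.

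On knowledge of the arm, section 5 (Randomization at First Group Session) says "the computer will randomly assign the participants to an arm, which will be recorded by staff in the locator database". Section 9 makes locator information the means of reaching men throughout follow-up, and adds "Staff will update the database with the new locator information". Section 8 asks staff to try to keep a man's own group facilitators from conducting his follow-up visits, and gives reporting bias as the reason. No section says that follow-up assessors are unaware of the arm.

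**The concern.** The outcomes are self-reports of unprotected anal sex and substance use. ACASI removes the listener. In a staff-administered telephone assessment a staff member takes part in the questioning, so the privacy described for ACASI no longer holds. The description of the call as staff-administered ACASI does not settle this, because ACASI is by definition a self-interview.

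If men report less risk to a person than to a computer, and do so to the same degree in both arms, a true effect is slightly diluted. If the degree differs by arm, a false difference appears or a true one is distorted. A difference is conceivable. One arm spends six sessions on sexual risk reduction and the other sees video-based content on other topics, and nothing stops a caller from knowing which arm the man was in. The protocol recognises this kind of bias for facilitators but adds no protection for the telephone route, where the interviewer's influence is greatest.

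**Working it through.** **Setting the sections side by side**

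1. Section 8: ACASI for all. Section 9: a staff telephone assessment for a defined subset. Both cannot stand as written.
2. Section 5: staff enter the arm in the locator database. Section 9: staff use and update locator information during follow-up. Neither says that the arm field is hidden.
3. Section 8: the facilitator rule is best-effort and covers only a man's own group. It is not limited to office visits, so it applies to calls too. A facilitator of another group may still make the call.
4. Section 2 (Data Analyses): the primary outcomes at 3, 6 and 12 months are compared between arms. Mode of assessment is not mentioned.

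**Scale**

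The plan gives no figure for this point, so there is none to reproduce. The 12-month numbers in Table 3 are the base: 4 × 213 = 852 and 4 × 298 = 1192, that is 852/2 = 426 to 1192/2 = 596 per arm.

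Assumed, because the protocol does not give them:
- f, the share assessed by telephone: 2%, 5% or 10% (from 0.02 × 426 = 8.5 to 0.10 × 596 = 59.6 men per arm)
- u, the between-arm difference in under-reporting among those men: 5, 10 or 20 percentage points
- outcome prevalence 0.5, two-sided 5% test, no allowance for group clustering

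Bias in the arm difference: b = f × u. Standard error: SE = √(2 × 0.25/n), which is 0.0343 for n = 426 and 0.0290 for n = 596. Type I error with bias b: P(Z > 1.96 − b/SE) + P(Z < −1.96 − b/SE).

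| f | u (points) | b (points) | Type I error, 426 per arm | Type I error, 596 per arm |
|---|---|---|---|---|
| 2% | 5 | 0.1 | 5.0% | 5.0% |
| 5% | 5 | 0.25 | 5.1% | 5.1% |
| 5% | 10 | 0.5 | 5.2% | 5.3% |
| 10% | 10 | 1.0 | 6.0% | 6.4% |
| 10% | 20 | 2.0 | 9.0% | 10.6% |

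For comparison, under the same assumptions the difference detectable with 80% power is about 9.6 points with 426 per arm and 8.1 points with 596 per arm. Allowing for clustering would widen the SE, which lowers the type I error figures and raises the detectable difference.

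If u = 0, no false difference arises. Suppose telephone captures a fraction r of true risk reports in both arms. The observed difference is then the true one times 1 − f(1 − r). With f = 10% the loss is at most a tenth of the true difference.

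**The case against.** - **Few men are affected.** It is tempting to read section 9 as sending every man who moves to the telephone. It does not: men who move near another project city and agree to transfer are assessed there, and the exclusion criteria remove men with a specific plan to leave within 15 months. This stands and narrows the point to the remaining movers.
- **Sight of the arm is not stated.** A reader might infer that callers see the arm. The protocol says only where the arm is stored. Its Data Management and Information Security sections limit the participant database to key staff. What remains is that nothing keeps the arm from the caller.
- **Lack of masking also affects office visits.** True, but there the man answers a computer in private, so the assessor has less influence on the answers.
- **Analysis by mode may be in a SAP that is not shown.** This stands. The protocol's silence does not show that telephone and ACASI records will be pooled without distinction, and the missing sensitivity analysis is not an error in itself. Masking and recording of mode are different: they are matters of conduct and data capture, and cannot reliably be restored afterwards.
- **Direction is unproven.** One might infer that the bias favours the intervention. Both arms receive personalised risk-reduction counselling at baseline, so both know the desirable answer, and the documents give no mode effect by arm.
- **Telephone data are better than missing data.** Agreed, and the fix keeps the telephone route.

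**Conclusion.** The contradiction between sections 8 and 9 is plain on the text. For a subset of movers, the self-reported outcomes are taken without the privacy of self-interview, by staff whom no rule masks to arm. Arm-dependent reporting bias is therefore possible in that subset.

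Its size and direction cannot be known from the documents, and it is probably small. With f and u each at 5-10% the shift is 0.25-1.0 point, and type I error is at most about 6.4%. The 9.0-10.6% figures need both a tenth of men telephoned and a 20-point difference in under-reporting between arms. The documents do not support the stronger readings that all relocated men are telephoned, that callers know the arm, or that the result is tilted towards the intervention. This is an inexpensive improvement to conduct, and not a threat to the primary comparison on any evidence in the protocol.

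**What to change.** 1. Reconcile sections 8 and 9: state in Follow-Up that telephone is the exception to ACASI and for whom, and replace the staff-administered ACASI wording with a description of how questions are put and answers entered.
2. Keep telephone as the fallback, but have calls made by staff from whom the arm field in the locator database is hidden and who did not facilitate that man's group.
3. Record the mode of administration on every follow-up record.
4. Report telephone use by arm, with one sensitivity analysis of the primary outcomes that excludes telephone records. This may sit in the SAP.

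The cost is a database permission setting, one variable, one extra analysis and a slight scheduling burden. No follow-up data are lost. Items 2 and 3 have to be in place before telephone data are collected.
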